# Risk management

## 12.1. Risk mitigation strategies

To minimise known harms, risks, and discomfort to participants, the below procedures will be implemented in the study. In both the control and intervention apps there is a help button that contains a directory of key sources of help such as phone numbers for Kids Helpline and LifeLine to ensure that participants have access to support 24/7. Participants are also reminded of contacting their GPs when feel distressed and maintaining their regular medicine during the trial.

In addition, there is a “get help now [panic button]” under this “help button”. When young people click the “get help now button”, a screen will pop up in the app to seek confirmation that they want to be contacted by a clinical psychologist during business hours. Once confirmed, a text message containing young people’s contact number will be sent to the clinical psychologist. They will be contacted by the clinical psychologist within the next 24 business hours.

In the middle of the trial (3-weeks after baseline assessment), young people will be asked to complete a safety check (approximately 1 minute) to assess their suicidal thoughts (using the SIDAS screener). If they report a SIDAS score above 20 they will be contacted by a clinical psychologist to refer them to appropriate psychological support, if they consent.

In addition, an independent Data Safety and Monitoring Board (DSMB) will be established to monitor the safety of research participants. DSMB membership will consist of 3 external members who are experts in clinical trial conduct, statistics, and youth mental health. The research team will record the number of notifications and notify the DSMB when each assessment period is complete. The DSMB will provide recommendations to the research team to continue, temporarily pause conduct of the trial, or discontinue, pending risk issues or adverse events. The research team will record all risk alerts in a case report which will be securely stored on the Black Dog Institute’s UNSW server.

The DSMB Charter is attached as Appendix E.

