**Roles and Responsibilities**

As outlined by NHMRC Guidance on “Safety monitoring and reporting in clinical trials involving therapeutic goods” (2016), the roles of the DSMB will be to assist in:

- safeguarding the interests of study participants
- ensuring that definitive and valid results are produced which will reliably inform future healthcare decisions
- enhancing the credibility of the trial.

These roles will be achieved by examining the data accumulated during the progress of the trial, ensuring risks and benefits are monitored, and that the trial remains safe for participants. The role of the committee is to review data completeness, adverse events, outcome data (unblinded if there is good reason for this) and to recommend to the trial committee whether the study requires modification.

Recommendations will be made to the TSG, which, if appropriate, will be shared by the trial team with the Sponsor and the HREC.

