**The DSMB will:**

- Following each assessment point, review aggregate subject data related to safety, attrition, withdrawals, data integrity and overall conduct of the trial and discuss via telephone conference;
- Provide recommendations to continue, modify or terminate the trial;
- Maintain records of all activities.

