**DSMB Meetings**

The first meeting

The members should review this charter and form an understanding of the protocol and study endpoints. Meetings will take place at an appropriate regularity decided by the DSMB committee. The DSMB will also meet if evidence from other research groups suggests potential for risk.

Meeting formats

DSMB meetings will be booked in for the week following the completion of data collection at each assessment point of the trial (baseline, post-intervention, 3-month post-intervention follow-up). Procedurally, when these set meetings are booked they will include both an open and closed session, however, it is up to the DSMB to decide if they would like to have a closed session. The typical structure of the meetings will first start with an open session involving both DSMB members, the trial leads, and the trial manager, followed by the closed session if needed. The meetings will be organised and chaired by either MT or JH. These meetings will generally be conducted by teleconference or videoconference, but the DSMB can decide whether they would like to do this face-to-face.

In the event of a closed meeting, unblinded data may be requested if there is a rationale (e.g. unexpected adverse events, aggregate data indicates self-harm above the rates expected from this group). Only DSMB members and others whom they specifically invite are present in closed meetings.

Outside of the pre-scheduled meetings, an extraordinary meeting may be called if a serious adverse event occurs. The trial leads or trial manager will report the event to the Chair within 24 hours of becoming aware of the event, and the Chair will convene a closed session meeting to discuss the event and make recommendations.

Following each meeting, a report minuting the open session including any DSMB recommendations and rationale for such will be prepared by the minute taker and sent to the CIA (MT) and all other members. For closed sessions, recommendations will be prepared by the Chair and sent to the Trial Lead (MT), who will present the outcomes at the TSG following each meeting. Meetings will occur until the trial concludes.

Reporting

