**Trial Stopping Guidelines**

The DSMB has the responsibility for deciding whether the trial should be stopped at any stage. They will do this if, and only if, two conditions are satisfied:

1. The results provide proof beyond reasonable doubt that the intervention is on balance definitely harmful, or for a particular category of, participants in terms of the major outcome; or is on balance, definitely having a therapeutic effect (noting that this is extremely difficult to assess without long-term follow-up periods).
2. The TSG are not conducting the project safely, which would include, but is not limited to, a failure to contact participants who flag as ‘at risk’ (scores >20 on the SIDAS) within the 48 hour period specified in the Duty of Care section within the Trial Protocol.

There is no plan to conduct any interim analyses, unless in cases where there is justification to unblind the data and condition (1) above is met. If this occurs, this DSMB Charter is in agreement with the Peto-Haybittle stopping rule whereby an interim analysis of a major endpoint would generally need to involve a difference between treatment and control of at least three standard errors to justify premature disclosure. An interim subgroup analysis would have to be even more extreme to justify disclosure. This rule has the advantage that the exact number and timing of interim analyses need not be pre-specified. In summary, the stopping rules require extreme differences to justify premature disclosure and involve an appropriate combination of mathematical stopping rules and scientific judgment.

#

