**DSMB Documentation and Communication**

1. Available information at open sessions

This will include routine study information (consent, completion, attrition), risk alerts, follow-up data, by group.

1. Available information at closed sessions

Unblinded data for SIDAS and suicide attempt data and statistical analyses for this data (including effect size estimates).

1. Blinding

If necessary, the DSMB will be provided unblinded data by the data officer.

1. Access to unblinded data

Only the DSMB members, trial leads and the trial manager have access to this data. The DSMB cannot share this beyond the committee to the trial team.

1. Who is responsible for circulating external evidence (e.g., from other trials, population-based

prevalence estimates)?

Trial manager, [name].

1. To whom will the DSMB communicate decisions and recommendations?

Within two weeks following each meeting, the DSMB will send findings and recommendations to the Trial Steering Group (TSG), listed on p. 5.

1. How are responses communicated back to the DSMB?

The TSG (Co-chaired by MT or JH) will review and respond to the DSMB recommendations if required. If the recommendations request action, the PI will provide a written response stating whether the recommendations will be followed and the plan for addressing the issues. Upon receipt, the DSMB will consider the TSG response and will attempt to resolve relevant issues, resulting in a final decision. The investigator will agree to disseminate the final decision to the appropriate regulatory agencies (TGA and HREC) within an appropriate time.

1. What happens to the reports after each DSMB meeting?

All DSMB members are asked to destroy reports after each meeting. Internal records will be kept by the data manager. Each report will add a table onto the previous one, and as such the reports will be cumulative.

1. What happens to minutes and records?

Any minutes should be kept by the Chairs until after the final trial analysis is complete, upon which point they should be shared with the Trial Manager for archiving for a minimum of 7 years.

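### The DSMB charter contradicts itself on who stops the trial, has the steering group's co-chairs chair DSMB meetings, and gives the board no route of its own past that group

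*Protocol*

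**What the plan says.** **Who decides.** Appendix E, Trial Stopping Guidelines: "The DSMB has the responsibility for deciding whether the trial should be stopped at any stage". One of the two conditions listed there is "The TSG are not conducting the project safely".

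**Who recommends.** Section 12.1: "The DSMB will provide recommendations to the research team to continue, temporarily pause conduct of the trial, or discontinue". The charter's own list of DSMB tasks: "Provide recommendations to continue, modify or terminate the trial".

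**What happens to a recommendation.** Appendix E, DSMB Documentation and Communication: "Within two weeks following each meeting, the DSMB will send findings and recommendations to the Trial Steering Group (TSG"). If action is requested, "the PI will provide a written response stating whether the recommendations will be followed". The DSMB then considers that response and a final decision results. The investigator passes it to the TGA and HREC, with no fixed time limit.

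**Who else hears of it.** Appendix E, Roles and Responsibilities: "Recommendations will be made to the TSG, which, if appropriate, will be shared by the trial team with the Sponsor and the HREC".

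**Who chairs.** Appendix E, DSMB Meetings: "The meetings will be organised and chaired by either" of two people given by initials. The same section identifies one of them as the Trial Lead, and DSMB Documentation and Communication names both as TSG co-chairs. Selection of the Chair describes a DSMB Chair whose job is to facilitate and summarise the board's discussions.

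**The concern.** A safety charter has to settle in advance who acts when the board concludes that the trial should pause or stop, who is told, and how fast. This one gives more than one answer to the first question. For the other two it relies on the people whose conduct may be the subject of the finding.

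Participants are young people with recent suicidal ideation, and suicide attempts are among the listed safety analyses. In an urgent case, staff following the charter could not tell whether the board's conclusion binds, who owns the final decision, or what the trial's status is until that decision is made. If the finding were that the TSG was running the trial unsafely, the board would have no written channel to anyone outside the TSG.

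**Working it through.** No power or error-rate calculation applies. The check sets the passages side by side.

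1. **Authority.** Trial Stopping Guidelines: the DSMB decides. Section 12.1, Roles and Responsibilities, and the DSMB task list: it recommends. DSMB Documentation and Communication: the PI states whether recommendations are followed, the DSMB reconsiders, and a final decision results. The last passage could be a bridge between the first two, but it does not say whose decision it is, by when it is due, or what the trial does meanwhile. The passages cannot all be operative.

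2. **Chairing.** DSMB Meetings assigns the chairing of DSMB meetings to either TSG co-chair. Selection of the Chair describes someone who facilitates and summarises the DSMB's discussions. DSMB Meetings itself treats the Chair as distinct from the Trial Lead: the Chair receives serious adverse event reports from the trial leads or manager, convenes the closed session, and sends its recommendations to the Trial Lead. Attendance at closed sessions is limited to members and their invitees. In practice the conflict therefore bears on open sessions, but the sentence on chairing is not confined to them.

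3. **Routing.** The recipient of issues and recommendations is the TSG (Reporting; DSMB Documentation and Communication). For closed sessions it is the Trial Lead, who presents the outcome to the TSG (DSMB Meetings). Onward sharing of recommendations with the sponsor and HREC is done by the trial team at its discretion (Roles and Responsibilities). The final decision goes to the TGA and HREC through the investigator, and the sponsor is not named at that step. No passage has the DSMB itself write to the sponsor or HREC. Because TSG conduct is a listed stopping condition, such a finding is addressed to its own subject.

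4. **Timing, for scale only.** The reporting window is 2 weeks × 7 = 14 days. Section 6.5 places the post-intervention assessment at day 42. 14 / 42 = 0.33, so the window is at most one third of the intervention period. The PI's response and the DSMB's reconsideration come after that and have no limit. By contrast, when a serious adverse event may prompt an extraordinary meeting, DSMB Meetings gives the trial leads or manager 24 hours to reach the Chair. No comparable time is set for a stop finding coming back.

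**The case against.** Much can be said for the charter, and several stronger readings do not survive it.

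- **A reader might infer that the PI can veto the board or keep a stop from the ethics committee.** The text does not say that. The PI's response is followed by DSMB reconsideration and a final decision that goes to the TGA and HREC. The discretion over sharing attaches to recommendations, not clearly to that decision. What remains is that the decision has no owner and no deadline.
- **A reader might infer that investigators preside over the board's confidential deliberations.** Closed sessions are limited to members and invitees, the Chair writes their recommendations, and closed-session decisions need a quorum of two. Members are external (Section 12.1) and must be cleared of significant conflicts. The charter itself claims only a degree of independence. Independence is weakened, not lost.
- **A reader might infer that a finding against the TSG could never reach the HREC.** Section 10.4 requires significant safety issues to be notified to the HREC. Section 11.4 and Table 2 send serious breaches to the HREC, and Section 11.4 also sends them to the sponsor's delegate. These routes are mandatory, but the DSMB does not send the reports, so they do not replace a route of the board's own.
- **A reader might infer that two weeks of further randomisation would follow a stop finding.** Scheduled meetings come after data collection at an assessment point is complete, and randomisation occurs on completing the baseline survey. Nobody is left to randomise after a scheduled meeting. Only an extraordinary meeting, or one that the board adds, could fall during recruitment. Nor can the two weeks be set against the 15-day limit in Section 10.4, because that clock starts when the sponsor instigates or becomes aware of the issue. Two weeks is also an upper limit, and nothing bars earlier communication.

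An advisory board reporting to a steering group is a legitimate arrangement. That stands too. The difficulty is that this charter also says the board decides.

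**Conclusion.** The point holds as a contradiction on stopping authority and a weakness in the board's independence. Three defects remain after the objections:

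- The charter has the board deciding in one place and only recommending in others, with an unowned, untimed final decision between them.
- TSG co-chairs are assigned to chair meetings of the board that judges the TSG, in conflict with the DSMB Chair described in the same charter.
- The board has no channel of its own to the sponsor or HREC, even when the finding concerns the TSG.

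The only figure is the reporting window: up to 14 days, at most one third of the 42-day intervention. The documents do not support an estimate of participants affected. The sample size and the planned analysis are untouched.

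The conclusion rests on the charter and Section 12.1 as written. How the DSMB Chair is appointed may be stated in parts of the appendix not available here. That would not remove the conflict over who chairs the meetings.

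**What to change.** Amend Appendix E, and align Section 12.1 where needed:

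1. State that the DSMB Chair chairs the DSMB's meetings. The TSG co-chairs may still organise them and attend open sessions.
2. Have the DSMB send any pause, stop or unsafe-conduct finding promptly and directly to the sponsor and HREC, in parallel with the TSG. Keep the two-week report for outcomes that let the trial continue.
3. Reconcile Trial Stopping Guidelines with Section 12.1, Roles and Responsibilities, the DSMB task list, and DSMB Documentation and Communication. Say whether the board decides or recommends, who owns the final decision and by when, and what the trial's status is until it is made. Which arrangement to adopt is for the sponsor and the board to settle.

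The cost is charter wording and its approval by the DSMB members. The sponsor and HREC may occasionally receive a finding that is later resolved without a stop. No change to the design, sample size or analysis is needed.

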# Summary of Changes from Version 1.0

[name], UNSW Coordinating Principal Investigator

Version 1.1 Modifications – Approved 14.03.2020

1. **Timing of final assessment**

The final assessment timepoint was changed from 4-months post-intervention to 3-months post-intervention to accommodate delays in the development of the LifeBuoy application.

**2. Changed the minimum eligible age of participants**

The minimum age for inclusion was changed from 16 year to 18 years.

**3. Changed wording on the PISCFs**

Wording was changing on the PISCFs to improve readability and to be consistent with changes to the timelines of assessment. The major changes to the PICF are pronoun changes, re-wording the form from the original third person perspective (‘participants’, ‘young person’) to a second person perspective (‘you’) to improve the readability of the form. The timing of the final assessment was updated to accurately reflect that it would be delivered at 3-months post-intervention.

Version 1.2 Modifications – Approved 20.04.2020

**1. Addition of new tertiary and ‘other risk’ measures**

**1.1. An additional two items relating to employment status will be included in the demographic section of the baseline questionnaire. We have added the following questions to the demographic section of the baseline questionnaire:**

1. What is your current employment status? (full-time| part-time| casual| self-employed| unemployed).
2. Has your current employment status changed as a result of the coronavirus (COVID-19) pandemic? (yes| no).

**1.2. COVID-19 related worry.** Ten items are used to assess the extent to which the coronavirus (COVID-19) pandemic influences participants’ perception of their symptoms (anxiety, depression, suicidal ideation) and coping strategies. The questions are as follows:

| Do you think the COVID-19 pandemic has increased your anxiety levels more than usual? |
| --- |
| Do you think the COVID-19 pandemic has increased your depression levels more than usual? |
| If you have had recent suicidal thoughts, do you think the COVID-19 pandemic has increased the frequency or severity of these thoughts? |
| If you were to develop flu-like symptoms tomorrow, would you be worried? |
| In the past one week, have you ever worried about catching COVID-19? |
| Please rate the current level of your worry towards COVID-19 |
| *(If Q6 response of 1 or 2 then skip to Q8)* What specific aspects of COVID-19 are worrying you? |
| Think about the strategies you normally use to feel better when you’re distressed*.* Do you think you have been using these strategies more, the same, or less since COVID-19? |
| In general, do you think these strategies have been less effective during COVID-19? |
| Have you noticed any symptoms improve during, or following, the COVID-19 pandemic? |

Items 1-3 relate to perceptions of symptoms and are rated on a five-point scale, ranging from ‘Not at all (1)’ to ‘All of the time (5)’ (e.g., ‘Do you think the COVID-19 pandemic has increased your anxiety levels more than usual’); items 4-6 relate to anticipated, experienced, and current worry and were modified from a previous study of pandemic related worry, with item 7 asking participants to indicate what aspects of COVID-19 are worrying them from a list of responses (e.g., ‘not knowing when the pandemic will end’); items 8-9 relate to the frequency and effectiveness of coping strategies used, from a list of 14 equally balanced healthy (e.g., ‘using social support’ and ‘relaxation techniques’) and unhealthy (e.g., ‘over-eating/comfort food’ and ‘avoidance/procrastination’) strategies. Participants are asked to rate their use of the strategies on a four-point scale (do not use, use less, use the same, and use more), and rate on a five-point scale whether they think each strategy used has been less effective during the pandemic, from ‘Not at all (1)’ to ‘All of the time (5)’. Item 10 asks participants to indicate if they have noticed any symptoms improve during or following the pandemic (none, yes - anxiety, yes – depression, yes – suicidal thoughts, yes – other).

**1.3. Uptake of the application.** The number of persons who downloaded the application they were allocated.
